### Sample Size Calculation

The sample size was calculated using G*Power 3.1.9.2 for testing the effect of the intervention by McNemar test. For 1-tailed hypothesis, at a power of 80% and level of significance of 0.05, a sample of 374 children is needed to detect a clinically important change in the proportion of children who will come back for their follow-up doses after introducing the intervention (ie, odds ratio of 1.5) [25]. After adjusting to potential proportion of lost to follow-up, the estimated sample size becomes 535. The analysis will be performed using Stata Statistical Software: Release 14 (College Station, TX: StataCorp LP.).

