### Study Design

This will be a cluster randomized controlled trial to evaluate the effectiveness of using an app to record the vaccination schedule, including reminders for parents, on increasing immunization coverage of Syrian children at the Zaatari refugee camp in Jordan. In March 2019, the study was announced through posters in Arabic, in the clinics. Clinicians and social workers will also inform the residents of the camps about the study. Parents interested in joining the study will be fully briefed about the study, and an informed consent form will be signed. After completing the consent form, participants (1) included in the app intervention arm (ie, children immunization app [CImA] recipients) will receive the usual care, access to the CImA app, and instructions on how to use it, in addition to updating their children vaccination card, or (2) under the usual care (control arm) of the trial, where they will receive the usual information on the benefits of vaccination, the child’s yellow vaccination card will be updated, in addition to the list of appointments for the future vaccines. The vaccination sites will be enrolled on the basis of convenience, because of the security situation in the refugee camp.

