### Intervention

The parents will be recruited to the study by trained volunteers at the 7 local clinics, providing vaccinations, around the Zaatari camp (Figure 1). Inclusion criteria will be the following: having at least one child of 0 to 5 years, being a local resident of the camp, and having an Android smartphone that can allow CImA app installation.

The intervention includes an app that will (1) allow storing Jordanian vaccination records (Table 1), per child, on the parents’ smartphones, in Arabic and English (in an interchangeable fashion), (2) have a set of automated reminders before the appointment of each child, and (3) in addition, summarize immunization records in the form of *due*, *taken*, or *overdue* appointments, labeled in orange, green, and red, respectively.

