### Statistical Analysis

The analysis will be done using a set of steps. The baseline characteristics of the participants will be compared between the intervention and control groups, using independent 2-tailed *t* test for continuous variables and Chi-square test for categorical variables. Delta analysis (D%) will be used to assess the change in the vaccination rate between preintervention (t0) and postintervention (t1), contrasting this change within the intervention and control groups. This will be complemented by an effect size assessment to quantify the difference in change between the 2 groups (Cohen *d* test will be used). Hierarchical level modeling will be conducted to consider any cluster effect of the clinics (defaulters will be treated as intent-to-treat analysis in the primary outcome of the study). For the secondary outcome, survival analysis will be used to further contrast the difference in the secondary outcome (proportion of defaulters) between the intervention and comparison groups, postintervention (t1). Stata will be used for the data analysis.

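### The stated 80% power (374 children, 535 after loss) is for an unclustered, paired McNemar test, not for the two-arm cluster randomised comparison that the trial makes

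*Protocol article*

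**What the plan says.** **Sizing** (Protocol article, Methods, Sample Size Calculation). G*Power 3.1.9.2 was used "for testing the effect of the intervention by McNemar test. For 1-tailed hypothesis, at a power of 80% and level of significance of 0.05". The result is 374 children, and the target is a change in the proportion "who will come back for their follow-up doses after introducing the intervention (ie, odds ratio of 1.5"). The number is then raised to 535 for loss to follow-up. No loss rate is given, no other inflation is mentioned, and it is not said whether 374 and 535 are totals or per arm.

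**Design** (Study Design). "This will be a cluster randomized controlled trial to evaluate the effectiveness of using an app to record the vaccination schedule". There is an app arm and a parallel usual-care arm.

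**Clinics** (Intervention). "The parents will be recruited to the study by trained volunteers at the 7 local clinics, providing vaccinations, around the Zaatari camp".

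**Analysis** (Assessments and Statistical Analysis). The outcome is the proportion returning on time for the follow-up visit. The change from t0 to t1 is contrasted between the two groups, and "Hierarchical level modeling will be conducted to consider any cluster effect of the clinics".

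**The concern.** McNemar's test compares two linked binary readings on the same child. It draws only on children whose status changed, and no control arm enters it. The trial will judge the app by a contrast between two sets of different children, grouped by clinic. That contrast has two further sources of variance that the calculation leaves out: sampling error in the control arm, and variation between clinics.

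This is a conflict between stated passages, not a detail missing from a condensed article. The test, the tails, the power, the effect size and the only inflation are all given, and they do not fit the design and analysis sections. At stake is the one quantitative promise the article makes about what the trial can detect. A reader who trusts the 80% would give a non-significant result more weight than it can bear.

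**Working it through.** **1. Can 374 be reproduced?** Not from the stated inputs alone, because the discordant proportion pD is not given. With d = pD(OR − 1)/(OR + 1), the McNemar normal approximation is

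N = [z(0.95)·√pD + z(0.80)·√(pD − d²)]² / d².

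At OR 1.5, d = 0.2·pD. With pD = 0.41, d = 0.082 and N = 375. With pD = 0.40, N = 385. The exact test gives 379 at pD = 0.43 and 370 at 0.44. So 374 is consistent with a one-sided McNemar test on a single set of pairs, and no arithmetic slip is shown.

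**2. Is a design effect hidden in 535?** 374/(1 − 0.30) = 534.3, rounded up to 535. A 30% loss (inferred) explains the whole step.

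**3. Power for a between-arm comparison.** From the article: OR 1.5, one-sided 0.05, 374, 7 clinics. Assumed: clinics are the randomised unit, 1:1 allocation, equal cluster sizes, a post-intervention comparison of two proportions, control return p0 of 25% to 80%, ICC 0 to 0.05.

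- Design effect: DE = 1 + (m − 1)·ICC, with m = N/7.
- Effective number per arm: n = (N/2)/DE.
- Power = Φ( (p1 − p0)/√{[p0(1 − p0) + p1(1 − p1)]/n} − 1.645 ).

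Worked case, p0 = 0.50, so p1 = 0.60 and the variance sum is 0.25 + 0.24 = 0.49:

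- ICC 0: n = 187, SE = √(0.49/187) = 0.0512, and 0.10/0.0512 = 1.953. Power = Φ(0.309) = 62%.
- ICC 0.02: m = 374/7 = 53.4, DE = 2.05, n = 91.3, SE = 0.0733, and 0.10/0.0733 = 1.365. Power = Φ(−0.280) = 39%.

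Over p0 = 25% to 80%, approximate one-sided power is:

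| Analysed | ICC 0 | ICC 0.01 | ICC 0.02 | ICC 0.05 |
|---|---|---|---|---|
| 374 in total | 43–62% | 32–48% | 27–39% | 19–27% |
| 748 (374 per arm) | 67–87% | 42–61% | 32–47% | 21–29% |

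The top of each range is at p0 = 40–50% and the bottom at 80%. If all 535 were a total and all were analysed, power is about 54–75% at ICC 0 and 20–54% for ICC 0.01 to 0.05. Using a pooled variance under the null moves these by less than one point.

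**4. Few clusters.** With 7 clusters in two arms, a t reference has 7 − 2 = 5 degrees of freedom. For 374 in total at ICC 0.01 it lowers 32–48% to about 27–39%.

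**5. Detectable difference, for illustration.** Take 374 analysed, 7 clinics, p0 = 0.50, ICC 0.02 (n = 91.3), two-sided 0.05 and 80% power. Solve Δ = k·√{[0.25 + (0.5 + Δ)(0.5 − Δ)]/91.3}.

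- Normal: k = 1.960 + 0.842 = 2.802, so Δ ≈ 0.20.
- t on 5 df: k = 2.571 + 0.920 = 3.490, so Δ ≈ 0.24.

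At p0 = 0.50 the target OR of 1.5 is a difference of 10 points.

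**The case against.** **It is a pilot, and the article condenses a fuller protocol.** The title does say pilot, and the Discussion promises only preliminary insight. Neither withdraws the explicit 80% claim. Leaving details to a fuller document explains a missing input, such as pD, but not a stated test that does not match the stated design.

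**The hierarchical model deals with clustering.** It gives an honest standard error. It does not restore the power that clustering removes.

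**374 may be per arm.** This is the strongest reply. On that reading, unclustered one-sided power is about 87% at 40–50% control return, so the paired basis alone would not sink the claim there. Clustering does, at every ICC from 0.01 up that was tried.

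**The planned contrast is of change from baseline, not post-intervention only.** True. The percentages above are illustrative, and baseline information could shift them either way. The article gives no basis for supposing that it would bring back 80%.

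**Stronger readings that the document does not support:**

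- *The sample-size arithmetic is wrong.* It is not shown to be wrong for the test named.
- *80% power is unattainable at any enrolment.* At p0 = 0.50 an unclustered total of about 606 is needed (2 × 2.487² × 0.49/0.10²). With 7 clinics the effective sample cannot exceed 7/ICC, so the ceiling binds once ICC is above about 0.0115. But that depends on an assumed ICC and on clinics being the randomised unit, which the article does not state.
- *The one-tailed test or the unstated pD is itself an error.* The first is openly declared and secondary here. The second may properly sit in the fuller protocol.
- *Children enrolled at first contact can have no pair.* The article does not say how a return visit before the intervention is defined, so this is inference.

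**Conclusion.** The concern holds as a mismatch between calculation and design. The 80% power for OR 1.5 describes an unclustered before-after test on pairs; the trial compares two arms of clustered children. That single-group reading of the calculation is inferred from the test and from the wording about change after the intervention; the article does not use the term.

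That 80% does not carry over holds for either reading of 374 at every control return from 25% to 80% and every ICC from 0.01 to 0.05 tried: power is 19–48% if 374 is the total and 21–61% if it is per arm. The exact size of the shortfall rests on the assumptions in step 3 of the working, none of which the article supplies except the 7 recruiting clinics. The claim should be corrected before results are interpreted, because it promises a property that the design has not been shown to have.

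**What to change.** Keep the planned enrolment and rewrite the Sample Size Calculation paragraph:

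1. Delete the claim of 80% power for an odds ratio of 1.5.
2. Say whether 374 and 535 are totals or per arm.
3. State power, or the detectable difference, for the between-arm difference in on-time return. Use the number analysed after loss, the number of randomised clusters, a design effect of 1 + (m − 1)·ICC over a range of ICCs, a t reference with degrees of freedom based on clusters, and a stated range of control return rates. The 20-point (normal) and 24-point (t, 5 df) differences above show the form of such a statement; they hold only for the inputs listed there.
4. In line with the title, present the effect estimate with its 95% confidence interval, and the estimated ICC, as the main products.

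The cost is one reworded paragraph and no extra children. The downside is that the stated power becomes much less favourable.

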### Intervention

The parents will be recruited to the study by trained volunteers at the 7 local clinics, providing vaccinations, around the Zaatari camp (Figure 1). Inclusion criteria will be the following: having at least one child of 0 to 5 years, being a local resident of the camp, and having an Android smartphone that can allow CImA app installation.

The intervention includes an app that will (1) allow storing Jordanian vaccination records (Table 1), per child, on the parents’ smartphones, in Arabic and English (in an interchangeable fashion), (2) have a set of automated reminders before the appointment of each child, and (3) in addition, summarize immunization records in the form of *due*, *taken*, or *overdue* appointments, labeled in orange, green, and red, respectively.

**Figure 1 figure1:**
[figure not shown]
The distribution of districts at the Zaatari camp and the location of the health facilities providing vaccinations. A complete map for the Zaatari camp can be found at https://data2.unhcr.org/en/documents/download/55994

**Table 1 table1:** Summary of the national vaccination schedule of the Jordan Ministry of Health.

Age	Recommended vaccines
1st contact	BCG^a^
2 months	DTaP-Hib-IPV + HBV^b^; RV^c^ 1st
3 months	DTaP-Hib-IPV + HBV; RV 2nd; OPV^d^
4 months	DTaP-Hib-IPV + HBV; RV 3rd; OPV
9 months	Measles; OPV
12 months	MMR1^e^
18 months	DTP^f^; MMR2; OPV
6 years (first grade)	Td^g^; Check for MMR; OPV

^a^BCG: Bacillus Calmette–Guérin.

^b^DTaP-Hib-IPV + HBV: diphtheria, tetanus, pertussis (whooping cough), polio, *Haemophilus influenzae* type b, and hepatitis B.

^c^RV: rotavirus vaccine.

^d^OPV: oral polio vaccine.

^e^MMR: measles, mumps, and rubella.

^f^DTP: diphtheria, tetanus, and pertussis.

^g^Td: tetanus and diphtheria.

### Children Immunization App Design and Security Clearance at Zaatari Camp

During the period from August to January 2019, the CImA app has been designed, developed in English and Arabic languages [26], and tested in house. In parallel to the app design and development, we have sought and obtained the security clearance from the office of the UNHCR, which has the full mandate of protecting the Zaatari camp.

### Assessments

Baseline will include the collection of our primary and secondary outcomes that are needed for the pre and postdata measurements. This includes social demographic data, any previous vaccination history, and electronic health literacy [27]. Participants, in both study arms, will be monitored for their follow-up visits to the clinic for the vaccination doses. The vaccination cards of both study arms will be marked as *intervention* or *control* arm; thus, the clinic nurses will notify the field workers about the follow-up visits. For the study outcome measures, we will measure any differences in the proportion coming back on time for the follow-up vaccination visit. The secondary outcome is the utility of the CImA app.

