**Methods:**

We developed and planned to test an app through a cluster randomized trial that will be carried out at the Zaatari refugee camp in Jordan. The study will be open to all parents who carry Android smartphones, have at least one child, and agree to participate in the study. The parents will be recruited to the study by trained volunteers at the vaccination sites around the Zaatari camp. Inclusion criteria will be the following: having at least one child of 0 to 5 years, being a local resident of the camp, and having an Android smartphone.

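### On-time return has no sound pre-intervention value for every child, so within-arm change and the paired sample size do not isolate the app's effect

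*Protocol article*

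**What the plan says.** All places are in the protocol article.

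- **Assessments:** "Baseline will include the collection of our primary and secondary outcomes that are needed for the pre and postdata measurements". The next sentence lists what this covers: "This includes social demographic data, any previous vaccination history, and electronic health literacy". The outcome measure named there is the proportion returning on time for the follow-up visit. The Objectives instead name vaccination coverage as primary and follow-up visits as secondary.
- **Sample Size Calculation:** 374 children for a one-tailed McNemar test at 0.05 with 80% power and an odds ratio of 1.5 for returning for follow-up doses once the app is introduced; 535 after allowing for loss to follow-up.
- **Statistical Analysis:** "Delta analysis (D%) will be used to assess the change in the vaccination rate between preintervention (t0) and postintervention (t1"), set against each other in the two arms. An effect size for the between-arm difference in change, a hierarchical model for clinics and a survival analysis of defaulters at t1 are also planned.
- **Intervention:** "The parents will be recruited to the study by trained volunteers at the 7 local clinics, providing vaccinations". Eligibility requires "having at least one child of 0 to 5 years, being a local resident of the camp" and a suitable Android phone.
- **Study Design:** the vaccination card is updated in both arms. There is a second route to the study: "Clinicians and social workers will also inform the residents of the camps about the study".
- **Table 1** ("Summary of the national vaccination schedule of the Jordan Ministry of Health"): contacts at first contact (no age given), 2, 3, 4, 9, 12 and 18 months, and 6 years.

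**The concern.** A paired test and a change score both need an outcome value before the app for each child. For on-time return, that means an earlier visit with a due date that the child kept or missed. Entry from birth, at clinics that vaccinate, leaves some children without such a visit. For others, it invites use of the enrolment visit, which the child reached by being there to be recruited.

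If the enrolment visit counts, children are partly selected on the outcome, and a later fall is built into both arms. If only earlier history counts, the youngest children, with the most doses still to come, leave the change analysis. In either case the change within one arm mixes age, schedule and selection with whatever the app does. The sample size rests on that same pairing.

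**Working it through.** **1. The plan's own figure.** Inputs from the Sample Size Calculation: OR 1.5, one-sided 0.05, power 80%.

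- Share of discordant pairs that are gains (not returning to returning): p = 1.5/2.5 = 0.6.
- Discordant pairs needed, normal approximation: (1.645 × 0.5 + 0.842 × √(0.6 × 0.4))² / (0.6 − 0.5)² ≈ 152.5, so 153.
- Total N = discordant pairs / pD, where pD is the discordant proportion. The article does not give pD. N = 374 implies pD ≈ 152.5/374 = 0.41. By the exact binomial method N is 379 at pD 0.43 and 370 at 0.44, so about 0.435. Over an assumed pD of 0.30 to 0.50 the exact N runs from 543 to 326.
- 374/(1 − 0.30) = 534.3, so 535. This fits if loss is 30%, which is not stated.

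So 374 and 535 are attainable but cannot be confirmed.

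**2. What 374 requires.** Gains are 0.6 × 153 ≈ 92 (normal) or 0.6 × 0.435 × 374 ≈ 98 (exact): about a quarter of the children must not have returned at t0 and have returned at t1.

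**3. Possible meanings of t0.**

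- *The enrolment visit, scored as attendance.* A child brought for a dose has attended. Such a child cannot gain, so if all were recruited this way the paired odds ratio would be 0/losses = 0, and 1.5 could not occur.
- *The enrolment visit, scored as on time.* A child who comes late has attended but was not on time, so gains are possible. They are confined to children recruited late for a dose.
- *Earlier history.* This is collected. A child at first contact has no earlier visit. A child at 2 months has at most first contact behind it, to which Table 1 gives no age. Neither has a t0 for on-time return. For older children t0 and t1 are different doses, and successive contacts from 2 to 18 months are 1, 1, 5, 3 and 6 months apart.
- *Coverage.* It can be read at baseline for more children, but cumulative coverage rises with age in both arms.

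**4. What survives when t0 is constant.** Suppose every child has t0 = 100%. The control return rates below are assumed, and the OR of 1.5 is borrowed as a between-arm odds ratio. App return is 1.5o/(1 + 1.5o), where o is the control odds.

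| Control at t1 | App at t1 | Change, control | Change, app | Difference in change |
|---|---|---|---|---|
| 50% | 60.0% | −50.0 | −40.0 | +10.0 |
| 60% | 69.2% | −40.0 | −30.8 | +9.2 |
| 70% | 77.8% | −30.0 | −22.2 | +7.8 |
| 75% | 81.8% | −25.0 | −18.2 | +6.8 |
| 80% | 85.7% | −20.0 | −14.3 | +5.7 |

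Within the app arm, a working app appears as a fall. Between arms, the constant cancels: −18.2 − (−25.0) = 81.8 − 75.0 = 6.8 points. The change score then adds nothing to the t1 comparison.

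**The case against.** The strongest reply is that the trial has a concurrent control arm and the plan uses it. The difference in change between arms removes a shared fall and shared drift with age, as step 4 shows, and the survival analysis at t1 needs no baseline value. This stands. A reader might infer that the planned analysis cannot measure what the app did; the documents do not support that.

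Two further inferences also fail. One is that t0 is fixed at 100% and no child can improve. The outcome in Assessments is on-time return, a late attender is not on time, and the app itself has an overdue status. Vaccination on the day is not an entry criterion, residents also hear of the study in other ways, and history or coverage can give a t0 for many older children. The other is to count first contact and 2 months as 2 of the 7 contacts up to 18 months and conclude that about 29% of children lack a t0. That assumes even recruitment over those contacts, while eligibility runs to 5 years and the article gives no age distribution.

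Finally, an article may leave the exact t0 rule and on-time window to the full protocol or SAP. That is fair for the definitions. It does not cover what the article itself fixes: a paired test as the basis of the sample size, and a change from baseline in an outcome that some eligible children cannot have at baseline.

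**Conclusion.** The point holds in a limited form. The plan relies on a pre-to-post change, yet on-time return has no sound t0 for children enrolled at first contact or at 2 months. Scoring the enrolment visit makes attendance near-certain by selection, and for the remaining children t0 and t1 are not the same quantity. Within-arm change and the paired McNemar basis therefore do not isolate the app's effect, and a change analysis drops the youngest children. The between-arm difference in change and the t1 survival analysis can still estimate the effect.

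On size, the 92 to 98 gains implied by 374 are out of reach only if t0 is attendance at the enrolment visit and children were brought for a dose that day. How many children lack a t0 cannot be worked out from the article. The return rates in the table, the discordant proportion and the 30% loss are assumptions.

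**What to change.** - **Assessments and Statistical Analysis:** state that the enrolment-visit dose does not count towards the outcome. Make the main analysis the between-arm comparison at t1 of on-time receipt of doses falling due after enrolment, within the hierarchical model for clinics already planned.
- **Baseline history:** read prior on-time history from the card before that day's update. Use it as a covariate with a category for no previous due dose, so that the youngest children stay in.
- **Within-arm change:** report it as descriptive only.
- **Sample Size Calculation:** state that the paired McNemar basis does not match this comparison.

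The changes are to wording, the data form and the analysis. History is already collected and the card is already handled at enrolment, so no new data source is needed. The price is the pre-post change as a headline figure, and some candour about size. For two independent arms with OR 1.5, one-sided 0.05 and 80% power, assumed control return of 50% to 80% needs 305 to 537 children per arm (610 to 1,074 in total) before any allowance for clustering, against the stated 374. Table 1 has no contact between 18 months and 6 years, so the text should also say that the denominator is children with a dose falling due during follow-up.

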## Introduction

### Background

Child immunization is a key component of the World Health Organization and the United Nations Children’s Fund (UNICEF)’s child survival intervention package [1]. Immunizing children is an essential strategy in the primary health care services, and it is a crucial public health objective. However, internationally, there are up to 19.4 million children who are still unvaccinated and face unnecessary deaths [2], especially among refugees [3]. Owing to this, refugees from conflict-torn countries have a high risk of acquiring Vaccine Preventable Diseases (VPDs) [4], especially as half of the refugees are below 18 years [5]. In conflict-torn countries, such as Syria, the immunization systems and follow-up, along with information systems, have been weakened, and herd immunity has been compromised. Before the crisis, Syria had greater than 80% of immunization coverage [6], which reduced to below 50% during the period 2011 to 2015. The total number of measles cases also increased from 13 to 740 in late 2011 and early 2013 (approximately an increase of 57-fold in less than 12 months) [2]. Since 2011, over 3 million children, aged 0 to 5 years, have fled out of Syria, to the Middle East and Europe [7]. These children have been exposed to several risky situations on the way to their new hosting countries, including passing or living in countries with low vaccination coverage [6]. In 2017, Roberton et al reported that the vaccination rate among Syrian children was 25% and 13% in Jordan and Lebanon, respectively [8]. Therefore, they are at a high risk of acquiring VPDs. This causes a heightened risk of unnecessary outbreaks in host countries, particularly among individuals who have not been vaccinated at all or completed vaccination schedules, whether refugee or from the host population [9]. The estimated cost of hospitalization may be up to US $25,000 per case [10]. The influx of children without clear immunization records therefore creates a challenge for health providers to maintain herd immunity and vaccinate unvaccinated children [5,9,11,12]. At the same time, the vaccination rate in the hosting country is considered low, for example, in Jordan, the vaccination rate among the general population is estimated to be less than 50% [13]. Given the risk to unvaccinated children, both in the refugee populations and the general population, it is paramount that support is given to health professionals to monitor and increase the rate of vaccination among refugee children. The challenge for monitoring vaccinations among refugees is compounded by the use of the yellow vaccination cards, which are easily lost or not brought to medical consultations. The field of mobile Health (mHealth) could be used as an alternative for paper-based vaccination records, and a smartphone app could present advantages to empower parents by informing them of vaccination schedules and dates and allowing them to monitor vaccination coverage on their own. There is growing evidence on the effectiveness of smartphone technologies in supporting health care services [14], though there remain gaps in the evidence of effectiveness. Smartphones provide a novel approach to solve problems with data registration, transmission, and storage [15-18]. Currently, there are over 5.2 billion users, in low- and middle-income countries [19]. The number of purchased cell phones is expected to exceed the total number of people on earth [20]. The emergence and spread of smartphones have provided a novel approach toward improving access to health care services [17]. The advancement of technology has provided tools that can empower users [21], patients, and other populations at risk. In general, mHealth can be useful among the population and among vulnerable groups, such as refugees [22]. Refugees and other vulnerable populations use smartphones as a survival kit, to connect with their social networks and to search for information about their host countries [10]. Anecdotally, women are the main caregivers for their children, and they are active users of smartphone technologies, so they can stay in touch with their social network and seek information regarding the integration process in the hosting countries [23]. It is therefore possible to use technological innovations, such as apps, to develop appropriate tools to support both women and men refugees, as well as health care professionals involved in the delivery of urgent health services. Health technology innovation is playing a crucial role in helping refugees, in various contexts around the world, including low-, middle-, and high-income countries [24].

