### Benefits for the Refugees

Few studies exist in the published literature, which focus on vaccination, health information, and the needs of refugee population [29,30]. This study will determine the immunization coverage gap and attempt to reduce it among refugee population in 3 different settings and evaluate a newly designed and piloted app to replace traditional paper-based immunization and health care records, which are not an option among a traveling/mobile population [31]. This will enable refugees to keep a record of vaccinations and prevent VPDs.

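### The one described route for recording follow-up visits is a nurse's notice prompted by an arm-labelled card, so reporting is unmasked and under-capture could differ by arm

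*Protocol article*

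**What the plan says.** In the protocol article, Assessments states that participants in both arms are monitored for follow-up visits and then gives the mechanism. "The vaccination cards of both study arms will be marked as" intervention or control; "thus, the clinic nurses will notify the field workers about the follow-up visits". The next sentence gives the outcome that rests on this: "we will measure any differences in the proportion coming back on time for the follow-up vaccination visit".

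Three other places bear on how well the card can serve as a trigger.

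- Background names as a monitoring problem "the use of the yellow vaccination cards, which are easily lost or not brought to medical consultations".
- Benefits for the Refugees describes "a newly designed and piloted app to replace traditional paper-based immunization and health care records".
- Study Design keeps the card in both arms. App recipients get the app "in addition to updating their children vaccination card", and for control children the "yellow vaccination card will be updated".

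The status of the outcome varies within the article. Assessments presents on-time return as the study outcome measure. Objectives and the Abstract make vaccination uptake or coverage primary and follow-up visits secondary. The Sample Size Calculation is built on the proportion returning for follow-up doses.

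**The concern.** There are two separate weaknesses.

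First, the nurse who starts the outcome record reads the allocation from the same document that prompts the report. In an unmasked trial of an app, a nurse or field worker may be more diligent in reporting, or in chasing, one arm than the other.

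Second, the wording makes the notice a consequence of the marked card. If the card is not shown, nothing in the described workflow tells the nurse that this child is in the study. A true return may then leave no trace in the study data. Parents who hold the record on a phone have less reason to carry paper, so the share of returns missed could differ between arms.

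The first weakness could favour the app and the second could hide its benefit. If both arms lost the same share of visits, the observed contrast would be only modestly diluted. If the shares differ, the contrast is biased, and the visit notices alone contain nothing that would show it.

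**Working it through.** **Textual check.** The article's stated figures do not test this point, so the first step is to set the sources side by side.

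| Possible source of visit data | What the article says of it | Same in both arms and free of the arm label? |
|---|---|---|
| Nurse notice (Assessments) | Prompted by the arm-marked card | No, the label is visible |
| End-of-study survey (Ethical Considerations) | Planned; not said to record visits or dates | Not stated |
| Review of the app schedule (Ethical Considerations) | Checked against the national schedule | No, possible only in the app arm |

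No clinic register or masked reader is named for visit dates.

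**Illustration of size.** The capture shares are assumptions; the article gives none.

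Inputs:
- True return rate: 50% in control, assumed, with 25% and 70% as a range.
- Capture: 95% in one arm and 85% in the other, assumed.
- Children per arm: 374 / 2 = 187, with 374 from the Sample Size Calculation and an equal split assumed. Clustering is ignored.

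Formulas: observed rate = true rate × share captured; odds ratio (OR) = [a/(1−a)] / [c/(1−c)], with a the observed app rate and c the observed control rate.

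*No true effect, 50% return in both arms, capture 95% app and 85% control:*
- a = 0.50 × 0.95 = 0.475; c = 0.50 × 0.85 = 0.425
- OR = (0.475/0.525) / (0.425/0.575) = 0.905 / 0.739 = 1.22
- Standard error of the difference = √[(0.475×0.525 + 0.425×0.575)/187] = √(0.49375/187) = 0.0514
- Shift = 0.05 / 0.0514 = 0.97. Chance of a 1-sided rejection at 0.05 = 1 − Φ(1.645 − 0.97) = 0.25, instead of 0.05.

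With capture reversed, OR = 0.82. For true rates of 25% and 70%, 95% app versus 85% control gives ORs of 1.15 and 1.35, with rejection of 0.14 and 0.41.

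*True rates 60% app and 50% control (OR 1.5):*

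| Capture, app / control | Observed rates | Observed OR |
|---|---|---|
| 95% / 95% | 0.570 / 0.475 | 1.47 |
| 85% / 95% | 0.510 / 0.475 | 1.15 |
| 95% / 85% | 0.570 / 0.425 | 1.79 |

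The 1.5 matches the value in the Sample Size Calculation only in number. That one is a McNemar odds ratio, whereas these compare the two arms.

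**Size of the look-up.** The plan's enrolment figure is 535. It is reproduced by 374 / (1 − 0.30) = 534.3, rounded up; the 30% loss is implied, not stated.

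**The case against.** The strongest reply is that this is a condensed article and that it describes one route without calling it the sole one. The full protocol may add a clinic register, and the end-of-study survey is not excluded as a source. That stands. A reader might infer that visits are captured only through the card, but the text supports no more than that this is the only route described.

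A reader might also infer that a child who returns without the card is counted as a defaulter. No section says so. Statistical Analysis mentions defaulters but does not equate a missing notice with default. The supportable statement is that such a return may go unreported.

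Differential card-carrying is plausible but not shown. The card stays in both arms, and the replacement of paper is described as an aim of the app, not as a trial procedure. The Background remark concerns medical consultations in general and gives no rate for vaccination visits. Reminders could equally make app parents better prepared.

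The event is a clinic visit, not a subjective rating, which limits what awareness of the arm can do to the content of a record. It does not limit what it can do to whether a report is made.

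Finally, if whole clinics are allocated, nurses may know the arm whatever the card says. That weakens the case for a neutral mark as a mask. It leaves the dependence on the card untouched and makes an arm-neutral source of dates more useful.

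**Conclusion.** The concern holds in a limited form. As described, the reporter of the on-time-return outcome sees the arm, and reporting runs through a card that the article itself calls unreliable. No arm-neutral source of visit dates is named. Under-capture could therefore differ by arm, with unknown sign.

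Under the assumed 95% and 85% capture with no true effect, the observed OR is about 1.22 or 0.82 at a 50% return rate. A true OR of 1.5 could appear as 1.15 or 1.79. These figures show sensitivity; they do not estimate the actual bias.

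A reader might conclude that the primary outcome is certainly misclassified. The article does not support that. It is inconsistent on whether follow-up visits are the main or the secondary outcome, and it does not say whether nurse notices feed the coverage measure. Nor is the problem beyond repair: missed visits can still be recovered before analysis if an independent record exists.

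**What to change.** 1. Mark cards not yet issued with a neutral study ID in both arms, and keep the arm in the study database only. Ethical Considerations already assigns ID numbers to participants, so a card so marked still identifies the child as enrolled.
2. Before analysis, have the existing field workers check all enrolled children in both arms against the sites' vaccination records, if the sites keep them, or against a list of enrolled IDs held at each site. Do this whether or not the card was shown.
3. Read the visit dates from a list that does not carry the arm, and use the recorded date as the outcome for every child.
4. State in Assessments which source supplies the visit date. If the full protocol already names a register, citing it would answer most of this point.

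The cost is a different mark and one look-up of about 535 children. The limits are these. The article does not mention site dose records, so their existence must be confirmed. A list of IDs helps only from the time it is in place. The Results section reports that enrolment is ongoing, so some cards may already carry the arm. If whole clinics are allocated, the neutral mark will mask nurses only in part, and the protection then comes mainly from the complete look-up.
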